## 6.6 Expected Duration of Trial

The end of the trial will be defined as the last patient's post 6 month visit telephone call. Each participant will remain on the trial until they have each completed the post 6-month visit telephone call. The study will run from December 2015 until December 2019 to ensure that each participant has 6 months of exposure to either the active or placebo treatment.

## 7. Trial Procedures

### 7.1 By Visit

Participants will receive a monthly dose of either Vigantol® Oil 120,000 IU per month (equivalent to 4,000 IU per day) or placebo administered by trained members of the research team.

Table 1: DFEND Trial Outcome Measures at Different Time-points

| STUDY PERIOD                                                                                            | SCREENING AND BASELINE | RANDOMISATION | TREATMENT Vigantol®/Placebo                                                                   | SAFETY CHECK  | ASSESSMENT VISIT                                           | FOLLOW UP PHONE CALL | SAFETY CHECK***** | ASSESSMENT VISIT***** |
|---------------------------------------------------------------------------------------------------------|------------------------|---------------|-----------------------------------------------------------------------------------------------|---------------|------------------------------------------------------------|----------------------|-------------------|-----------------------|
| VISIT Name                                                                                              | Baseline VISIT         |               | DOSING VISITS 1 – 6                                                                           | 3 MONTH VISIT | 6 MONTH VISIT                                              | POST 6 month CONTACT | 9 MONTH VISIT     | 12 MONTH VISIT        |
| TIMEFRAME                                                                                               | WEEK -2                | WEEK 0        | Monthly for 6months (Visit 1 is the anchor date, Visits 2 to 6: -2/+2 weeks from anchor date) | MONTH 3       | MONTH 6 (Visit 6 assessment: -4/+6 weeks from anchor date) | POST 6 mth           | 9 MONTHS          | 12 MONTHS             |
| Eligibility & Informed consent                                                                          | X                      |               |                                                                                               |               |                                                            |                      |                   |                       |
| Sociodemographics                                                                                       | X                      |               |                                                                                               |               |                                                            |                      |                   |                       |
| NOS (Duration of Untreated Psychosis)                                                                   | X                      |               |                                                                                               |               |                                                            |                      |                   |                       |
| Current medication                                                                                      | X                      |               | X                                                                                             | X             | X                                                          |                      |                   |                       |
| Medical history                                                                                         | X                      |               |                                                                                               |               |                                                            |                      |                   | X                     |
| Vitamin supplementation                                                                                 | X                      |               | X                                                                                             | X             | X                                                          |                      |                   |                       |
| Anthropometrics                                                                                         | X                      |               |                                                                                               |               | X                                                          |                      |                   | X                     |
| Blood sampling: vitamin D concentration (storage)                                                       | X                      |               |                                                                                               |               | X                                                          |                      |                   | X                     |
| Blood sampling: incl. clinical, genetic, cardiovascular and inflammatory markers                        | X                      |               |                                                                                               |               | X                                                          |                      |                   | X                     |
| Urine pregnancy test                                                                                    | X*                     |               | X*                                                                                            | X*            | X*                                                         |                      |                   |                       |
| Smoking habits                                                                                          | X                      |               |                                                                                               |               | X                                                          |                      |                   | X                     |
| PANSS                                                                                                   | X                      |               |                                                                                               | X             | X                                                          |                      |                   | X                     |
| GAF                                                                                                     | X                      |               |                                                                                               |               | X                                                          |                      |                   | X                     |
| CDS                                                                                                     | X                      |               |                                                                                               |               | X                                                          |                      |                   | X                     |
| OPCRIT                                                                                                  | X                      |               |                                                                                               |               |                                                            |                      |                   |                       |
| Sun Exposure questionnaire                                                                              | X                      |               |                                                                                               |               | X                                                          |                      |                   | X                     |
| IPAQ                                                                                                    | X                      |               |                                                                                               |               | X                                                          |                      |                   | X                     |
| SIMPAQ                                                                                                  | X                      |               |                                                                                               |               | X                                                          |                      |                   | X                     |
| Fitzpatrick Skin Type Questionnaire                                                                     | X                      |               |                                                                                               |               |                                                            |                      |                   |                       |
| Vitamin D Food Frequency Questionnaire                                                                  | X                      |               |                                                                                               |               | X                                                          |                      |                   | X                     |
| Randomisation                                                                                           |                        | X             |                                                                                               |               |                                                            |                      |                   |                       |
| Adverse events recorded **                                                                              | X                      |               | X                                                                                             | X             | X                                                          | X                    | X                 | X                     |
| Blood sampling for calcium levels (including parathyroid hormone test if calcium is above normal range) | X                      |               | X***                                                                                          | X             | X                                                          |                      | X                 |                       |
| Administration of IMP or Placebo                                                                        |                        |               | X****                                                                                         | X****         | X****                                                      |                      |                   |                       |
| Patient Medication Guess                                                                                |                        |               | X                                                                                             | X             | X                                                          | X                    | X                 | X                     |
| Service Contacts Form                                                                                   | X                      |               |                                                                                               |               | X                                                          |                      |                   | X                     |

\* In the event that it is not possible to obtain a urine sample, a blood HCG sample will be obtained and tested for pregnancy. No IMP will be administered without first ascertaining pregnancy status. Pregnancy tests will not be done for female participants who are permanently sterile or who are post-menopausal (no menses for 12 months without an alternative medical cause).

\*\* AEs collected from consent. Patients will be phoned 28 days post the last dose of treatment at 6 months to check for any adverse events. At dosing visits 1 – 6, we will assess adverse events in person with the participant at their scheduled visit. If no IMP is given at the Month 6 visit, no follow-up call will be needed. Should a participant withdraw from the study, AEs will need to be collected up to 28 days after their last dose.

\*\*\* Blood sampling for calcium levels (including parathyroid hormone test) will only be performed at these time points if patient reports nausea and vomiting.

\*\*\*\* The IMP is administered once a month, every month for 6 months.

\*\*\*\*\* The 9-month safety check and 12-month assessments will only be performed on those patients who have received more than 6 monthly doses of the IMP prior to the protocol change dated (02.06.17). However, the IMP/placebo will no longer be administered after 6 months.

DFEND Protocol Version 10.1 03.05.2019

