We will also ensure that all patients are made aware of the symptoms of hypercalcaemia (loss of appetite, nausea and vomiting, constipation and abdominal pain, increased thirst and frequent urination, fatigue, weakness, and muscle pain). If any of these symptoms are detected in between dosing visits, patients will be advised to contact their GP, so that their GP can arrange for a blood test for hypercalcaemia (and report hypercalcaemia as a suspected adverse reaction to the Trial Coordinating centre). First line treatment for hypercalcaemia is simple rehydration but if this is not effective then pharmacological interventions can be used. The GP will advise of this. The research team who administer the monthly IMP/placebo dose will also ask the patient if they have experienced any of these symptoms since they were last seen by the research team, this will be done routinely every month before any IMP/placebo administration. Should these symptoms be reported at a scheduled visit, a blood test will be offered to the patient to check calcium levels and ensure patient-safety.

Participants will be asked to refrain from taking vitamin D supplements (including multivitamins containing vitamin D); however, supplementation of up to 400IU/day will be permitted throughout the trial, as recommended by Public Health England.

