## 5.7 Concomitant Medication

No restrictions are placed on the prior or concomitant interventions (medications or therapies, rescue or subsequent treatments) allowed, other than we ask the participants to refrain from taking vitamin D supplements (including multivitamins that contain vitamin D) that exceed 400IU/day for the duration of the trial. At each treatment visit (once monthly for 6 months) and at the final assessment, researchers will ask the participant if they are taking any additional vitamin D supplements. If the participant indicates that they have been taking additional vitamin D supplements that exceeds 400 IU/day, a blood sample will be collected and tested for calcium. If the corrected calcium is above normal range, a parathyroid test will be performed. The participant will be asked to refrain from taking further vitamin D supplements that exceed 400IU/day and if they decline to do so, they will be encouraged to stay involved in the study for the full duration but no more IMP/placebo will be administered.

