## DFEND

|                                                                                               |   |   |      |      |      |   |
|-----------------------------------------------------------------------------------------------|---|---|------|------|------|---|
| Randomisation                                                                                 |   | X |      |      |      |   |
| Adverse events recorded                                                                       |   |   | X    | X    | X    | X |
| Blood sampling for calcium levels (including parathyroid hormone test if Calcium is abnormal) | X |   | X**  | X    | X    |   |
| Administration of IMP or Placebo                                                              |   |   | X*** | X*** | X*** |   |
| Patient Medication Guess                                                                      |   |   | X    | X    | X    | X |
| Service Contacts Form                                                                         | X |   |      |      | X    |   |
| Patient Medication Guess Form                                                                 |   |   | X    | X    | X    | X |

\* In the event that it is not possible to obtain a urine sample, a blood HCG sample will be obtained and tested for pregnancy. No IMP will be administered without first ascertaining pregnancy status. Pregnancy tests will not be done for female participants who are permanently sterile or who are post-menopausal (no menses for 12 months without an alternative medical cause).

\*\* Blood sampling for calcium levels (including parathyroid hormone test) will only be performed at these time points if patient reports nausea and vomiting.

\*\*\* The IMP is administered once a month, every month, for 6 months.

Note: The 9-month safety check and 12-month assessments will only be performed on those patients who have received more than 6 monthly doses of the IMP prior to the protocol change dated (02.06.17). However, the IMP/placebo will no longer be administered after 6 months.

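### The schedule footnotes allow dosing-visit calcium tests only for nausea and vomiting, in conflict with protocol sections 5.7 and 5.3

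*Combined protocol and SAP*

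**What the plan says.** In protocol Table 1 (section 7.1), the calcium row has plain marks at baseline, Month 3 and Month 6. The mark for dosing visits 1 to 6 carries a footnote saying that sampling "will only be performed at these time points if patient reports nausea and vomiting". The schedule in SAP section B has the same sentence under its own calcium footnote: "Blood sampling for calcium levels (including parathyroid hormone test) will only be performed at these time points if patient reports nausea and vomiting".

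Four other protocol sections say when calcium is to be checked:

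- **Section 5.7.** On extra vitamin D, it states: "At each treatment visit (once monthly for 6 months) and at the final assessment, researchers will ask the participant". If reported use is at a level "that exceeds 400 IU/day, a blood sample will be collected and tested for calcium". No symptom is needed. Table 1 also marks its "Vitamin supplementation" row at the dosing visits.
- **Section 5.3.** Staff ask about a full list of hypercalcaemia symptoms, and "this will be done routinely every month before any IMP/placebo administration". The action is: "Should these symptoms be reported at a scheduled visit, a blood test will be offered to the patient to check calcium levels". For the time between visits: "If any of these symptoms are detected in between dosing visits, patients will be advised to contact their GP".
- **Section 8.2.** Calcium is checked at further times when there is evidence of hypercalcaemia symptoms, with no limit to particular ones.
- **Section 9.1.** It lists the symptoms and sets more frequent testing for nausea, vomiting or both.

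**The concern.** The footnote uses the word *only*, so it cannot be read as a partial list that sits beside the wider rules. It describes what happens at the dosing visits, and those are the visits at which 5.3 and 5.7 tell staff to ask about symptoms and supplements. A participant who reports marked thirst, or supplements above 400 IU/day, would be tested or offered a test under one part of the protocol but not under another.

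The protocol treats these triggers as relevant to safety. Section 5.3 calls for serum calcium monitoring in long-term treatment above 1000 IU a day, and the trial dose is equivalent to 4,000 IU a day. The same section advises particular caution when other vitamin D is taken as well, which is the case that 5.7 covers and the footnote leaves out. Sites that work from the schedule and sites that work from the text could monitor calcium differently.

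**Working it through.** No figure in the plan is in question. The check sets the triggers side by side, counts what the footnote leaves out, and counts the visits where this matters.

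**1. Triggers compared**

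| Place | Trigger | When it applies | Force |
|---|---|---|---|
| Table 1 footnote; SAP section B footnote | Nausea and vomiting, exclusively | Dosing visits | Limits testing |
| Protocol 5.7 | Supplements above 400 IU/day, no symptom needed | Asked at each treatment visit | Required |
| Protocol 5.3 | Any listed symptom | Scheduled visits; asked before each dose | Offered |
| Protocol 8.2 | Any evidence of hypercalcaemia symptoms | Additional times, dosing visits not named | Bloods to be taken |
| Protocol 9.1 | Nausea, vomiting or both | More often than baseline and three months | To be performed |

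The conflict with 5.7 is the clearest: that test is required, depends on no symptom, and follows a question asked at the treatment visit. The conflict with 5.3 is also direct, because section 5.6 schedules a dosing visit each month, so dosing visits are scheduled visits. Sections 8.2 and 9.1 support the point but are less specific.

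**2. Symptoms left out.** Section 9.1 names ten, and 5.3 names the same ten: (1) nausea, (2) vomiting, (3) appetite loss, (4) constipation, (5) pain in the abdomen, (6) thirst, (7) passing urine often, (8) fatigue, (9) weakness, (10) pain in the muscles. The footnote covers two of them:

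10 − 2 = 8 symptoms left out, plus the supplement trigger.

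If the *and* in the footnote is read strictly, nausea alone or vomiting alone would not qualify either, and none of the ten would lead to a test as a single symptom. Section 5.3 also writes the two as a pair, so 8 of 10 is the fairer count.

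**3. Dosing visits with no unconditional calcium test.** There are six monthly doses. Table 1 has unconditional tests at baseline (Week −2), Month 3 and Month 6.

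- Doses at Months 0 to 5: {0, 1, 2, 3, 4, 5} without {3} leaves {0, 1, 2, 4, 5} = 5 visits. The baseline sample is taken before randomisation at Week 0, so it is not a test at the Month 0 dosing visit.
- Doses at Months 1 to 6: {1, 2, 3, 4, 5, 6} without {3, 6} leaves {1, 2, 4, 5} = 4 visits.

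The range is therefore 4 to 5 visits per participant.

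**4. Number of tests missed.** The documents give no rate for these symptoms or for supplement use above 400 IU/day, so this cannot be calculated.

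**The case against.** The strongest reply is that the footnote has no precedence over the text. Sections 5.3 and 5.7 give direct instructions to the same trained staff and remain in force. The footnote could also be read as governing only a scheduled sample, with tests for cause handled separately. Section 5.7 does not say that the sample is taken at the visit where use is reported, 5.3 says only that a test is offered, and 8.2 does not name dosing visits. There are other safeguards too: corrected calcium above 2.6 mmol/L and a known history of hypercalcaemia are exclusions, the dose was chosen as one considered safe in pregnancy, and participants are told the full symptom list and directed to their GP between visits. SAP section B records what data are collected and does not direct clinical testing.

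Much of this stands, and it limits the consequence. It does not remove the conflict. No routine calcium sample is planned at the dosing visits, so the footnote is itself a rule for testing on cause, and it names one cause as the only one. Reading it as silent about other causes goes against its wording. The SAP copy matters less than the protocol footnote, but it repeats the same error and should be corrected with it.

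A reader might go further and infer that the footnote blocks the tests, or that staff would not do them. The documents do not support that. They contain two instructions that disagree and no rule on which prevails, so the supported statement is that tests could be omitted.

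**Conclusion.** The point holds as an internal inconsistency in a safety-monitoring rule. Both footnotes are narrower than 5.7 and 5.3, and also narrower than 8.2 and 9.1. They leave out the required supplement-triggered test and 8 of the 10 listed symptoms. This matters at 4 or 5 dosing visits per participant, depending on whether the first dose falls at Month 0.

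The conclusion rests on three assumptions: that *only* is meant as written, that dosing visits count as scheduled visits under 5.3, and that the unconditional marks in Table 1 are carried out as shown.

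The size is modest. Sections 5.3 and 5.7 still apply, and three calcium tests are unconditional. A reader might infer that hypercalcaemia would go undetected, or that the trial's results are at risk. Neither follows: the documents give no basis for counting missed tests, and the primary analysis and sample size do not depend on them. It is still worth correcting, because an operative safety instruction contradicts a test that the protocol requires.

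**What to change.** Replace the calcium footnote in protocol Table 1 and in SAP section B with wording such as:

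*At dosing visits, calcium will be tested if the participant reports vitamin D supplement use above 400 IU/day (section 5.7), and a test will be offered if any hypercalcaemia symptom listed in section 5.3 is reported; PTH will be tested if calcium is above the normal range.*

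This keeps the difference between the required test in 5.7 and the offered test in 5.3. It also restores the condition on the parathyroid hormone test that the row label in Table 1 already carries. Simply putting a longer list after *only* would lose that difference.

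In 7.1(f) and 9.1, replace the nausea and vomiting trigger with any symptom listed in 5.3.

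The cost is a wording change in the protocol and the SAP. No visits are added, and the dosing-visit tests are ones that 5.3 and 5.7 already promise. The analysis does not change.
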